## Background

### Opioid overdose risk among justice-involved women

Risk for drug-related death is significantly elevated in the 4 weeks following release from prison (Merrall et al., 2010). Among adults released from Washington State prisons between 1999 and 2003, the all-cause risk of death in the 2 weeks post release was 12.7 times greater than for other residents, and drug overdose was the leading cause of death after release (Binswanger et al., 2016). Drug overdose death after release from incarceration has been linked to multiple individual and social determinants. Individual risk factors for overdose include a decrease in drug tolerance while incarcerated due to no drug access or access to low purity drugs (Merrall et al., 2010). Risks of overdose are further elevated when heroin is used with other substances (e.g., alcohol, benzodiazepines, and other depressants) (Coffin et al., 2007), there is presence of comorbid medical disorders (e.g., HIV and mental health disorders) (Coffin et al., 2007), and there is a history of prior overdose (Coffin et al., 2007) or injection of drugs (Merrall et al., 2010). Formerly incarcerated individuals, moreover, may be exposed to socio-cultural norms or behaviors that encourage drug use (i.e., drug use to celebrate release). Little to no access to treatment facilities, a lack of social networks, and homelessness also increase overdose risk (Merrall et al., 2010).

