**Fig. 1 Fig1:**
[figure not shown]
Conceptual model for ROAR pilot evaluation

Aim 1 collects participant survey data, completes qualitative interview data, and abstracts medical charts to assess: 1) Implementation Outcomes, 2) Service Outcomes, and 3) Client Outcomes. Implementation outcomes examine acceptability, adoption, engagement and retention in the ROAR pilot. Aim 2 evaluates the effects of the ROAR program on our primary outcome of any opioid overdose. This is a binary outcome indicating a fatal or non-fatal opioid-related overdose event in the 6 months following release from incarceration.

#### Aim 1

Pilot the ROAR intervention to reduce risk of overdose among adult women released from prison. ROAR is offered to all eligible female inmates being released to one of Oregon’s four most populated counties over the 18-month recruitment period. The pilot (*n* = 100) includes a process evaluation using quantitative and qualitative measures grounded in the Consolidated Framework for Implementation Research (Keith, Crosson, O'Malley, Cromp, & Taylor, 2017). Baseline participant surveys assess history of overdose, lifetime mental health status and current depression using the Patient Health Questionnaire-9 (PHQ-9). Three-month and 6-month followup surveys of participants assess self-reported return to opioid use, non-fatal opioid overdose and engagement with SUD treatment and recovery support services. Qualitative interviews with participants, CRMs, and clinicians assess barriers and facilitators to retention in treatment and acceptability of the intervention.

#### Aim 2

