Evaluate the effect of the ROAR pilot on opioid overdose among adult women released from prison. We evaluate the association between participation and the primary outcome of opioid overdose, including either a fatal or non-fatal overdose event. Fatal and non-fatal opioid overdoses are assessed for all adult females released from prison during the 18-month study period (expected *n* = 1000) regardless of participation in the ROAR intervention. Using administrative data provided by the Oregon Department of Corrections (e.g., dates of incarceration) and Oregon Health Authority (i.e., Medicaid claims and encounters), we compare the odds of overdose among participants versus a comparison group of previously incarcerated adult females with documented addiction or dependence in administrative records. Data from the comparison group will consist of de-identified administrative data for fatal and non-fatal overdoses in the state. The study will not directly recruit for this group. Statistical analyses adjust for county- and patient-level confounders including level of substance abuse treatment need and mental health treatment need assessed at prison intake.

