#### Baseline Surveys and Assessments

During the informed consent/baseline data collection visit with the ROAR staff, participants are asked to complete baseline surveys, which provide individual characteristics that will be used to describe study participants and explore factors potentially associated with implementation and client outcomes. The Baseline Survey collects demographic information, medical status, overdose experiences, psychiatric status and mental health treatment, and PHQ-9 responses. Selected items from the Addiction Severity Index Lite (ASI Lite) will assess an individual’s history related to substance use, family/social status, employment, and medical and psychosocial issues.

*Questionnaires Included in Baseline Survey:*PHQ-9Participant DemographicsASI Lite (selected items)

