#### Analysis

##### Opioid Overdose

The primary outcome, opioid-related overdose, is measured using administrative (Medicaid claims, hospital discharge data) and vital statistics. We use hospital discharge data to supplement Medicaid claims data in the event that participants lose or change Medicaid enrollment. The validity of administrative data to identify opioid-related overdose is high (sensitivity = 97%, specificity = 85%) (Green et al., 2019). We use Oregon vital statistics (death certificate data) to ascertain opioid-related fatalities. Oregon has a centralized medical examiner model which is known to provide more consistent and specific reporting of drugs implicated in fatalities (Buchanich, Balmert, Williams, & Burke, 2018; Warner, Paulozzi, Nolte, Davis, & Nelson, 2013).

Our primary analysis will examine the effect of pilot participation on the rate of fatal and non-fatal overdose events. We will calculate person-years of follow-up using the time between release date and subsequent death or study conclusion. Thus, women will contribute to calculations of person-years once they are released, except during subsequent incarcerations or after fatality. We will censor follow-up at the end of Quarter 10 or the date of incarceration if they were in prison as of this date. Our primary outcome (any opioid overdose) will be modeled as a rate with person-years as an offset variable.

We will employ either a mixed logistic model if the outcome turns out a non-rare event, or a mixed poisson model (with poisson approximation to binomial distribution) if the outcome turns out to be a rare event. The effect of ROAR participation will be examined by testing the slope coefficient (i.e., b1, see below) of the main treatment effect variable (ROAR participation yes/no) in the model. We will also adjust the treatment effect using covariates such as age, race/ethnicity, incarceration time, and mental health level of treatment need while incarcerated. We control for correlation due to clustering at county level by including a random effect (i.e., α, see below) in the model.

*Alternatively, the model described below is employed for our analysis:*

g[E(y|x)] = b0 + b1*ROAR,+b2*x + α, where g(.) is a link function (e.g., logit or log link), and b2 is a slope coefficient vector of adjusting covariates included in the model; α is the random effect account for county specificity.

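### Prior overdose, a risk factor the article itself names, is in no stated adjustment set for the ROAR versus comparison analysis, and the primary-model covariate list does not repeat the substance abuse treatment need promised elsewhere

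*Protocol article*

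**What the plan says.** All references are to the protocol article.

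- **Risk factor.** The Background section on overdose risk says that risk is further raised when "there is a history of prior overdose".
- **How it is measured.** Under Aim 1, "Baseline participant surveys assess history of overdose, lifetime mental health status and current depression". The section on baseline surveys agrees: "The Baseline Survey collects demographic information, medical status, overdose experiences, psychiatric status and mental health treatment, and PHQ-9 responses". Table 2 places the baseline overdose item at the consent visit, which only ROAR participants attend.
- **Comparison women.** Under Aim 2, "Data from the comparison group will consist of de-identified administrative data for fatal and non-fatal overdoses in the state", and "The study will not directly recruit for this group".
- **Adjustment, Aim 2.** "Statistical analyses adjust for county- and patient-level confounders including level of substance abuse treatment need and mental health treatment need assessed at prison intake". The Limited Administrative Dataset section makes the same commitment.
- **Adjustment, primary model.** The Opioid Overdose analysis section says: "We will also adjust the treatment effect using covariates such as age, race/ethnicity, incarceration time, and mental health level of treatment need while incarcerated". The list is given as examples, and the model equation carries a generic covariate vector.

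**The concern.** The ROAR effect on overdose comes from a non-randomised comparison. The Discussion relies on multivariable regression to deal with imbalance between the groups, so the choice of covariates is the main protection against confounding.

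Prior overdose is an obvious candidate: the article names it as a predictor of the outcome. Yet it appears in no stated adjustment set, and the one planned measurement exists in only one of the two groups. The groups are also defined differently on addiction. ROAR women must meet DSM-5 criteria for moderate or severe OUD, while the Limited Administrative Dataset section asks only for a documented SUD in comparators. If overdose history differs between the groups and is left out, the estimated ROAR effect carries that difference.

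A smaller matter sits beside it. The section that specifies the primary model does not repeat a confounder that two other sections say will be adjusted for. Someone programming from that section alone could omit it.

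**Working it through.** The plan gives no figure to reproduce here. The check sets the statements side by side and then illustrates the possible size.

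**1. Which confounders are named where**

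| Variable | Aim 2 | Limited Administrative Dataset | Opioid Overdose analysis |
|---|---|---|---|
| Substance abuse treatment need | named, at intake | named, at intake | not named (open list) |
| Mental health treatment need | named, at intake | named, at intake | named, while in prison |
| Age, race/ethnicity, incarceration time | not named | not named | named |
| Prior overdose | not named | not named | not named |

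The exploratory analysis screens baseline characteristics at p < 0.25, but it is a search for predictors of overdose and does not define the adjustment set for the ROAR effect.

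**2. Could the survey variable be used?** No. It is collected at the ROAR consent visit, and comparison women are never surveyed.

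**3. Could the groups differ on opioid severity?** The ROAR recruitment list was itself built on documented SUD. Table 3 shows that 68 of the 140 women interviewed at pre-screen did not meet moderate to severe OUD: 68/140 = 48.6%. A comparison group selected on SUD could be similarly mixed. The Discussion, however, calls the comparators women with OUD. If they are in fact restricted to OUD, the gap would be smaller.

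**4. Illustrative size.** For a binary confounder with prevalence P1 in ROAR women and P0 in comparators, and risk ratio R for overdose, omission multiplies the observed risk ratio by

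B = [1 + P1(R − 1)] / [1 + P0(R − 1)].

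P1, P0 and R are all assumptions. The true risk ratio of 0.40 is the benchmark in the Sample Size and Power section.

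| P1 | P0 | R | B | True 0.40 appears as |
|---|---|---|---|---|
| 40% | 20% | 3 | 1.8/1.4 = 1.29 | 0.51 |
| 35% | 25% | 3 | 1.7/1.5 = 1.13 | 0.45 |
| 40% | 30% | 1.5 | 1.2/1.15 = 1.04 | 0.42 |
| 60% | 30% | 4 | 2.8/1.9 = 1.47 | 0.59 |
| 20% | 40% | 3 | 1.4/1.8 = 0.78 | 0.31 |

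The last row reverses the first, for the case where ROAR women are the lower-risk group. These are crude factors. Adjustment for intake substance abuse need could absorb part of the bias.

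**5. Room for more covariates.** With 100 comparators and the assumed 20% to 25% per year, six months gives 100 × 0.20 × 0.5 = 10 to 100 × 0.25 × 0.5 = 12.5 expected comparison events. At a risk ratio of 0.40, 100 ROAR women would have 4 to 5. Events are few, so each added term has a price.

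**The case against.** A reader might infer that addiction severity goes unadjusted altogether. The article does not support that. Aim 2 and the Limited Administrative Dataset section both commit to adjusting for substance abuse treatment need at intake, and the primary-model list is open. The three statements can be read as compatible, and the exact covariate list is often left to an analysis plan that is not shown here. This reduces the second part of the point to a matter of alignment.

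A reader might also see a conflict between mental health need at intake and the same need while incarcerated. Intake is part of incarceration, and nothing says that a different score is used or that timing differs by group.

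The ROAR-only survey is not in itself an error. Its stated purpose is to describe participants and explore factors related to implementation and client outcomes, not to adjust the group comparison.

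It is tempting to say that the omission must hide a benefit. Selection also runs the other way. ROAR women volunteer and are willing to start medication and community care, and women whose illness would make participation hazardous are excluded. In Table 3 (multiple response), among 79 women ineligible after interview, 68 were not interested in treatment and 36 would not consider medication.

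Finally, the article does not show that pre-incarceration records are already held, and its Discussion concedes that residual confounding may persist.

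What remains is that prior overdose is in no stated adjustment set. An open list does not plan for a variable that needs its own look-back period and a common definition, and admitting residual confounding does not replace adjusting for a named risk factor that may be obtainable.

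**Conclusion.** The point holds in two limited parts. First, prior overdose is a risk factor named in the article, is absent from every stated adjustment set, and is planned to be measured only in ROAR women, in a form the comparative model cannot use. An administrative equivalent is unplanned, not shown to be impossible. Second, the primary-model covariate list does not repeat the substance abuse treatment need promised in two other sections, and these should be aligned. Because that need score is not described as opioid-specific, including it may not fully capture overdose history.

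The size is unknown. Under the assumed inputs where ROAR women carry more prior overdoses, the observed risk ratio is inflated by a factor of about 1.04 to 1.47. With the imbalance reversed in one example, the factor is 0.78. These figures rest wholly on assumed prevalences and risk ratios, and neither the net direction nor the magnitude can be settled from the article. It is a worthwhile improvement to a non-randomised comparison and does not show that the analysis is invalid.

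**What to change.** In the Opioid Overdose analysis section:

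1. Name the intake level of substance abuse treatment need as a covariate, matching Aim 2 and the Limited Administrative Dataset section.
2. Add any opioid overdose before the index incarceration. Define it identically in both groups from Medicaid claims and hospital discharge data, the sources already used for non-fatal overdose, over one fixed look-back (for example, 12 months).
3. State that the survey-reported overdose history stays out of the comparative model and is used for ROAR-only description and exploration.

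The cost is a longer look-back in the data request and two explicit model terms, one of them already promised. Pre-prison records will be incomplete for women not then on Medicaid, and overdoses without a hospital or Medicaid encounter will be missed in both groups. Some precision is lost with so few events. A comparison group larger than 100 would ease this: the article sets 100 as a minimum and expects about 1,000 releases in all.

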### Preliminary enrollment and retention data

Enrollment and retention data for the first 7 months of recruitment are summarized in Fig. 3. At the time of publication, new enrollments were paused due to the Coronavirus (COVID-19) pandemic. Oregon Department of Corrections closed its facilites to non-essential staff and suspended all  visiting on March 13, 2020. Enrolled ROAR participants continued to receive follow up medical treatment and remote CRM services via secure video conference, phone, email, and text. Research check-ins, 3-month and 6-month follow-up surveys, and qualitative interviews continued by phone or secure videoconference.

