##### Limited Administrative Dataset

Fatal and non-fatal opioid overdoses will be assessed for all women released from prison during the 18 month study period (expected *n* = 1000) regardless of participation in ROAR. Using administrative data provided by the Oregon Department of Corrections and the Oregon Health Authority, study staff will compare odds of overdose among ROAR participants (expected n = 100) versus a comparison group of at least 100 previously incarcerated adult women with a documented SUD who are released into Oregon counties that are not participating in ROAR. Multivariate statistical analyses will be conducted to adjust for county and patient level cofounders including level of substance abuse and mental health treatment needs assessed at intake.

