## Discussion

Oregon is well-positioned to successfully pilot and maintain a new model of pre-release linkage to MOUD and CRM services for incarcerated individuals. The state has a lengthy history of demonstrated support for peer mentor services and a network of more than 1,200 CRMs. Oregon Medicaid covers peer support services and has an established peer training and certification program overseen by Oregon’s addiction professional licensing board and an active peer professional association. In 2017, a statewide expert workgroup developed a peer supervision competency guide and a best practice guide for forensic peer specialists working with individuals with criminal justice involvement. Similar to many other states, however, standardized pre-release peer linkages have not been established for incarcerated individuals. In 2017, Oregon’s Governor Kate Brown established a statewide opioid taskforce with a focus on increased access to opioid agonist and antagonist therapy and overdose prevention. The taskforce sponsored a successful bill providing funds to study and address barriers to MOUD and strengthen peer recovery support programs. The legislation requires the Oregon Health Authority, Department of Corrections, and Department of Consumer & Business Services to collaborate to identify these barriers to MOUD.

 ROAR's pragmatic evaluation plan has a number of inherent limitations. Our analysis of opioid-related overdoses using administrative data is an observational cohort design. Although we use a concurrent comparison cohort of women with OUD released into non-ROAR counties as a comparison group, these women may systematically differ in ways related to our outcomes. We attempt to mitigate this limitation by using multivariable regression models to control for potential imbalance, but residual confounding may persist. We will be circumspect when reporting findings from this analysis and acknowledge this limitation.

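### ROAR status is fully nested in county, so b1 compares two sets of counties: the county random effect does not remove a mean gap between them, and release period is partly confounded as well

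*Protocol article*

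**What the plan says.** **Where ROAR runs.** Protocol article, Aim 1: "ROAR is offered to all eligible female inmates being released to one of" Oregon's "four most populated counties over the 18-month recruitment period". Release to a participating county is also an inclusion criterion.

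**Where comparators come from.** Limited Administrative Dataset describes women "with a documented SUD who are released into Oregon counties that are not participating in ROAR". The Discussion describes "a concurrent comparison cohort of women with OUD released into non-ROAR counties as a comparison group". The Abstract, Aim 2 and Sample Size and Power describe the comparison group with no county restriction.

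**How county is handled.** Analysis, Opioid Overdose: "We control for correlation due to clustering at county level by including a random effect". The covariates it offers as examples are age, race or ethnicity, time incarcerated and mental health need. Aim 2 says: "Statistical analyses adjust for county- and patient-level confounders". Limited Administrative Dataset repeats this. In both places the examples are substance use and mental health need recorded at intake.

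**Calendar time.** Preliminary enrollment and retention data reports that "new enrollments were paused due to the Coronavirus (COVID-19) pandemic", and that prison access closed on 13 March 2020. The length of the pause is not given. Comparators are women released over the same 18-month period. No release-date term is named in the model.

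**The concern.** Aim 2 is to evaluate the effect of ROAR on overdose, and b1 is the estimate that carries it. If no county contains both ROAR women and comparators, b1 is a contrast between the four largest counties and other counties. Differences between those sets, for example in local overdose rates or treatment supply, would enter b1 alongside any programme effect. They could imitate a benefit or hide one. The text nevertheless says that county-level confounders are adjusted for. A difference in release period between the groups could act in the same way if release date is left out of the model.

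**Working it through.** The plan states no county gap, so there is no figure of its own to reproduce. Table 4 concerns detectable differences and is used here only for its range of within-county correlation (0 to 0.01).

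**1. Nesting.** Pilot counties supply only ROAR women to the comparison. Under Limited Administrative Dataset and the Discussion, all other counties supply only comparators. There is no within-county contrast.

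**2. What b1 estimates.** The model is g[E(y|x)] = b0 + b1·ROAR + b2·x + α. Let θ be the true ROAR effect and δ the mean difference on the link scale between pilot and comparison counties, given x. ROAR equals the pilot-county indicator for every woman, so b1 estimates θ + δ. The intercept α has mean zero and is assumed independent of ROAR. It widens the standard error of b1 but does not absorb δ. County fixed effects would not help, because the four pilot-county indicators sum to the ROAR column.

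**3. Illustration with θ = 0.** The assumed risks of 20% and 25% borrow the baseline range in Sample Size and Power.

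- Odds ratio = (0.20/0.80)/(0.25/0.75) = 0.250/0.333 = 0.75, and ln 0.75 = −0.288.
- Risk ratio = 0.20/0.25 = 0.80.

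The mixed logistic model was then simulated with 4 pilot counties of 25 women and 10 comparison counties of 10 (an assumed split). The random-intercept SD was 0.182, so the latent correlation is 0.182²/(0.182² + π²/3) ≈ 0.01. Each row has 400 runs.

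| Pilot risk | Comparison risk | Mean b1 | OR | Rejection at 5% |
|---|---|---|---|---|
| 20% | 20% | 0.020 | 1.02 | 3.8% |
| 20% | 25% | −0.292 | 0.75 | 11.8% |
| 20% | 30% | −0.546 | 0.58 | 32.0% |
| 20% | 15% | 0.397 | 1.49 | 17.0% |

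In the second row the simulated b1 (−0.292) matches the raw log odds ratio (−0.288), so the random effect removed none of the gap. The Monte Carlo standard error there is √(0.118 × 0.882/400) = 1.6 points. A further set of 1,500 runs, which included an uneven split (55/20/15/10 against 20 counties of 5), gave an OR of 0.74 and 12%.

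The plan's 20% and 25% are annual rates, while the outcome window is 6 months. Halving both gives (0.10/0.90)/(0.125/0.875) = 0.78. With 100 per group and a two-proportion test without clustering, the null SE is √(0.1125 × 0.8875 × 2/100) = 0.0447 and the SE under the gap is also 0.0447. Rejection is Φ((0.025 − 0.0876)/0.0447) + Φ((−0.025 − 0.0876)/0.0447) ≈ 8.6%. The same formula gives 13.5% for 20% against 25%.

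**4. Calendar period.** Assume a start on 1 June 2019, so 13 March 2020 is at month 9.4. Assume even releases, 6 months of follow-up each and, as a worst case, no ROAR release after that date.

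- ROAR person-time after the closure: (6²/2)/(6 × 9.4) = 18/56.4 = 32%.
- Comparators over 18 months: (18 + 8.6 × 6)/(6 × 18) = 69.6/108 = 64%.
- With a pandemic rate multiplier k and no ROAR effect, the rate ratio is [1 + 0.319(k − 1)]/[1 + 0.644(k − 1)]. This is 1.08, 0.94, 0.88 and 0.80 for k = 0.8, 1.2, 1.5 and 2.0.

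The multipliers are assumed. Consent may precede release by up to 90 days, so ROAR releases could have run to about month 12.4. The ROAR share would then be (18 + 3 × 6)/(6 × 12.4) = 36/74.4 = 48%, and the ratio at k = 2 would be 1.484/1.644 = 0.90. Both groups have releases before the closure, so period is only partly confounded.

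**The case against.** Several points on the other side are sound.

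- The Analysis section offers the random effect for correlation, which is a correct use. It does not call it confounding control. The fault lies in the separate county-adjustment statements, which nothing in the text carries out.
- The Discussion calls this an observational cohort, says the comparison women may differ and that residual confounding may persist, and promises careful reporting. That is real disclosure. However, it offers multivariable regression as the mitigation and does not say that exposure and county set coincide.
- The covariate list is open, and a SAP that is not shown may add to it. That could supply county covariates or release date. It cannot create a within-county contrast.
- The sections without a county restriction would allow same-county comparators. This is a conflict to resolve. Same-county non-participants would restore a within-county contrast but bring volunteer selection.

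A reader might also infer four stronger claims that the documents do not support.

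- *County covariates can never help.* Non-overlap is certain only for population size. Overlap on overdose rate or treatment supply is unknown.
- *The pandemic period cannot be separated from ROAR.* It can be, through release date. The length of the pause and any restart are not stated.
- *Four treated counties make the test of b1 clearly anti-conservative.* At a correlation of 0.01, the top of the plan's range, simulated rejection with no gap was 3.8% in one set of runs and 5.2% to 5.5% in another. Material inflation needs larger correlations than the plan considers.
- *20% against 25% is the actual county gap.* That range expresses uncertainty about one baseline rate for the power calculation.

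**Conclusion.** The point holds in this limited form. If the comparators are those of Limited Administrative Dataset and the Discussion, ROAR is fully nested in county. Then b1 is the ROAR effect plus any mean county-set difference left after the covariates. The random effect does not remove that difference, and the stated county-level adjustment is not delivered as written, because every named covariate is patient-level.

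The size of the bias is unknown. A 5-point gap, taken purely as an illustration, gives an OR of about 0.75 and about 12% rejection with no ROAR effect. This rests on the assumed risks and county split. Calendar period is a second, lesser and adjustable source of bias, with a size that depends on how long the pause lasted and on how overdose rates changed.

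**What to change.** **(a)** Match comparators to ROAR women on release quarter, or add release quarter to the model. Release dates are already needed for person-years. Matching discards some comparators, but there is room. Applying the plan's 40% opioid-history figure to the roughly 30 monthly releases outside the pilot counties gives 12 a month, or 12 × 9.4 ≈ 113 by 13 March 2020, against the minimum of 100.

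**(b)** Reconcile the comparator definition: the Abstract, Aim 2 and Sample Size and Power against Limited Administrative Dataset and the Discussion. Settle at the same time whether the criterion is documented SUD or OUD.

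**(c)** In Aim 2 and Limited Administrative Dataset, replace the county-adjustment claim with a statement that b1 compares two sets of counties and cannot by itself separate ROAR from county-set differences. Add named, measured county covariates such as the pre-period county overdose rate. With four pilot counties only very few can be supported.

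**(d)** Test b1 with small-cluster degrees of freedom. This is a safeguard and does not address the county gap.

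**Optional sensitivity analysis.** Report a pilot-county by period contrast, using women released before June 2019 from the same data sources. It addresses county differences that are stable over time. It needs a wider data pull and gives a wider interval.

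Items (a), (b) and (d) and the statement in (c) change only wording and analysis. The county covariates need some extra county-level data.
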